## Background

Prolactin-producing pituitary adenomas typically cause functional hyperprolactinaemia, which is characterised by galactorrhoea and hypogonadism, and may therefore result in subfertility [1]. Additionally, non-specific symptoms, such as fatigue, and psychological and neurocognitive complaints have been described [1]. Although a rare condition, prolactinomas account for over half (32–66%) of all pituitary adenomas [1]. Prolactinomas are found 3 times more frequent in women than in men with a peak incidence between the age of 25 and 35 years [2, 3]. The majority of prolactinomas are subcategorised, based on the size on magnetic resonance imaging (MRI), as microprolactinomas (< 10 mm; 80%), but they may also present as macro (10–40 mm) or giant (> 40 mm) and invasive tumours, which may compromise visual function due to compression of the optic chiasm, nerves, or tracts [2].

Prolactinoma treatment is primarily targeted at reduction of symptoms and restoration of gonadal status and fertility by normalising prolactin levels [4]. As it is a highly effective and non-invasive treatment option, medical treatment with a dopamine agonist (DA) is recommended as first-line treatment for almost all prolactinoma patients, while endoscopic transsphenoidal resection is reserved for those patients with (severe) DA intolerance or in case of DA-resistant prolactinoma [4].

Although DA treatment results in normalisation of prolactin levels, and subsequent reduction of symptoms in 81% of patients, the 2-year remission rate after DA withdrawal remains low (34%) and, therefore, long-term medical treatment should be expected [5]. DA treatment is usually well tolerated, although orthostatic hypotension and gastrointestinal complaints are frequently reported as side effects. DAs are furthermore associated with psychological side effects, which are mild in 40%, but more severe in up to 5–10% of patients [5–13]. Particularly, impulse control disorders (ICDs), e.g. pathologic gambling, are acknowledged as a typical side effect [13–16]. The heterogenous pattern of side effects and prolactinoma symptomatology may (in part) explain that both untreated (symptomatic) and medically treated prolactinoma patients have reported a decreased physical and mental health-related quality of life (HRQoL) [5, 17–22].

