#### Inclusion criteria

At least 18 years of ageA history of signs and symptoms matching with prolactinomaHyperprolactinaemia, defined as a prolactin level ≥2 times the local laboratory maximum, present at the time of enrolment (PRolaCT-1) or present < 12 months before enrolment (PRolaCT-2 and PRolaCT-3)No clear alternative explanation for hyperprolactinaemia, e.g. medication usePresence of a clearly identifiable pituitary mass on MRI not invading the cavernous sinus and with a maximum diameter ≤25 mm. A representative MRI at the time of randomisation is required. This MRI should generally not be older than 12 months in PRolaCT-3 and 2 months in PRolaCT-1 and PRolaCT-2Defining inclusion criteria for the three RCTs are:
PRolaCT-1: no prior prolactinoma treatmentPRolaCT-2: prior DA treatment for 4–6 months orPRolaCT-3: prior DA treatment for at least 2 years and having conducted at least one withdrawal attempt within 12 months prior to study recruitment (if the withdrawal attempt took place > 6 months before study inclusion, another withdrawal attempt is performed before randomisation to confirm prolactinoma persistence)

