##### Analyses in PRolaCT-O using propensity score methods

As the treatment groups in PRolaCT-O may differ at baseline, propensity score methods will be used to account for potential confounding. The propensity to receive surgical counselling will be estimated using logistic regression including potential confounders such as duration and effectiveness of prior DA treatment, the amount and severity of side effects to DA treatment measured at study entrance measured with the PRO-CTCAE, age at inclusion, gender (male or female), type of centre treatment takes place (secondary or tertiary), physician enrolling the patient (endocrinologist, gynaecologist, or neurosurgeon), prolactinoma size (micro- or macroadenoma), patient and MDT treatment preference pre- and post-counselling (neutral, medication, or surgery), and the likelihood of positive surgical outcome (unlikely, possibly, or likely) as estimated post hoc by two neurosurgeons blinded to received treatment. Adequacy of the propensity model will be assessed by checking if standardised mean differences after propensity adjustment are below 0.10 and by inspecting balancing plots.

Inverse probability weighting based on the propensity score will be used to balance the treatment groups. After observations are reweighted, treatment groups are compared in the same way as in the RCTs. Propensity matching will be used as a sensitivity analysis.

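### The PRolaCT-O propensity model enters tumour size as micro or macro although diameter in mm is on file, which can leave confounding by size in the remission comparison

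*Protocol article*

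**What the plan says.** The protocol article, under Analyses in PRolaCT-O using propensity score methods, says that the propensity to receive surgical counselling "will be estimated using logistic regression including potential confounders such as duration and effectiveness of prior DA treatment", among others. The list is therefore open. The form of one item is nevertheless given outright: "prolactinoma size (micro- or macroadenoma"). The same list holds patient and MDT treatment preference and "the likelihood of positive surgical outcome (unlikely, possibly, or likely) as estimated post hoc by two neurosurgeons blinded to received treatment".

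The weights are inverse probabilities from this model. Adequacy is judged by standardised mean differences below 0.10 and by balancing plots. Then "After observations are reweighted, treatment groups are compared in the same way as in the RCTs". Under Main endpoints, that comparison is an analysis of covariance with the baseline measurement for the MHS, and a chi-square test without covariates for remission.

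The Inclusion criteria, which also apply to PRolaCT-O, require a representative MRI and set an upper limit of 25 mm on maximum diameter. A diameter therefore exists for each patient.

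**The concern.** On the protocol's own account, size is likely to affect both treatment choice and remission. The Background singles out tumours of limited size as those most likely to be resected completely. Study design expects patients with adenomas that are hard to resect to be among those who decline randomisation. The Discussion expects confounding by indication in PRolaCT-O.

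A split at 10 mm treats all microadenomas as alike, and all tumours from 10 to 25 mm as alike. Differences in diameter within each class are not weighted away unless another covariate happens to carry them. For the MHS, the outcome model adds adjustment for the baseline score. For remission nothing follows the weights, so residual imbalance in size goes straight into the estimated difference.

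PRolaCT-O matters beyond its own report. It is the stated fall-back for the primary objectives if recruitment is difficult, it is expected to report before the RCTs, and it enters the combined meta-analysis with them. A bias in its remission estimate would carry over into the pooled result.

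**Working it through.** The plan gives no figure on this point, so there is none to reproduce. The checks below use assumed associations and show only what the two-class form can do.

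**1. Share of bias removed by a two-class split.** For a standard normal covariate cut at its p-quantile c, adjusting for the class removes a share φ(c)² / [p(1 − p)] of the bias, where p is the share with a microadenoma.

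- p = 0.5: c = 0, φ = 0.399; 0.159 / 0.25 = 0.64
- p = 0.7: c = 0.524, φ = 0.348; 0.121 / 0.21 = 0.58
- p = 0.8: c = 0.842, φ = 0.280; 0.0784 / 0.16 = 0.49
- p = 0.9: c = 1.282, φ = 0.175; 0.0308 / 0.09 = 0.34

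The Background puts microprolactinomas at 80% of all prolactinomas. The share in PRolaCT-O, which requires a clearly identifiable, non-invasive mass, is not given, hence the range.

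**2. Effect on remission when size is the only item in the weights.** Simulation with 400,000 patients and no true treatment effect. Assumed log-odds per SD of size: −0.6 for surgical counselling and −0.7 for remission.

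| | 50% micro | 80% micro |
|---|---|---|
| Size SMD, unweighted | 0.53 | 0.53 |
| Size SMD, weighted on micro/macro | 0.19 | 0.27 |
| False remission difference, unweighted (points) | 7.9 | 8.0 |
| Weighted on micro/macro (points) | 2.7 | 3.9 |
| Weighted on continuous size (points) | about 0 | about 0 |

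The SMD falls by 1 − 0.19/0.53 = 64% and 1 − 0.27/0.53 = 49%, as in step 1. With continuous size the SMD is about 0.

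**3. Adding the neurosurgeons' rating.** The protocol's model is richer than size alone, so a three-level rating correlated with size was added to micro/macro, again with assumed slopes.

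- If size acts on treatment choice only through what the rating captures, at most 0.4 points remain.
- If size also acts directly on choice, 2.1 to 3.8 points remain with a size–rating correlation of 0.5 to 0.9, against 2.9 to 4.2 for micro/macro alone.
- With a correlation of 0.3 to 0.7, 2.4 to 2.8 points remain at 50% micro and 3.3 to 4.1 at 80% micro.

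The treatment preferences were not modelled and could lower these figures further. Together the runs give roughly 0 to 4 points.

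**4. Scale.** The sample size section assumes 90% against 50% remission, with up to 30% of the intervention arm not operated: 0.7 × 90 + 0.3 × 50 = 78%, a difference of 28 points. Four points is 4/28 = 14% of that. With 110 per group, the unweighted standard error of the difference is √[(0.78 × 0.22 + 0.50 × 0.50)/110] = 6.2 points. The upper end is thus below one standard error, but unlike sampling error it does not shrink with more patients.

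**5. Baseline MHS.** In the simulation of step 2, treatment choice also depended on baseline MHS (log-odds −0.5 per SD), which was left out of the weights. The weighted MHS difference was biased by about −3.6 points without baseline adjustment, and by no more than 0.1 point with the planned weighted analysis of covariance.

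**The case against.** The strongest reply is that the model does not rest on micro/macro alone. The blinded rating of likely surgical outcome and the recorded preferences are plausible routes by which size steers treatment choice. If they capture that route fully, little bias remains. This stands, and it is why the lower end of the range is 0. It does not settle the matter, because the rating has three levels and is made post hoc, so those who chose the treatment did not have it.

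A second reply is that functional forms belong in the analysis plan, and that the 10 mm cut matches the RCT stratification. The first part would hold if the article were silent, but it states the form. Stratified allocation needs classes; a propensity model does not.

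Three stronger readings are tempting, and the documents do not support them.

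- A reader might infer that baseline MHS is left uncontrolled because the list does not name it. It is a covariate in the weighted analysis of covariance for the HRQoL endpoint.
- A reader might infer that baseline prolactin is excluded although measured at entry in everyone. The list is open, and "duration and effectiveness of prior DA treatment" may carry part of the same information. The qualifying value, "defined as a prolactin level ≥2 times the local laboratory maximum", must be present at enrolment only for PRolaCT-1 type patients; for pretreated patients it may be up to 12 months old.
- A reader might infer that the 0.10 check would pass while diameter stays unbalanced. The article does not restrict the check to the covariates as modelled, and it adds balancing plots. It does not say that continuous diameter will be checked either.

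**Conclusion.** The point holds for tumour size and for the remission endpoint. The plan discards millimetre information that eligibility already requires, in an analysis where the weights are the only control of confounding. A two-class split removes about 64% of size-related bias at 50% micro and about 49% at 80% micro, if size is roughly normal on the scale that matters. The resulting false remission difference is roughly 0 to 4 points. That range rests on assumed slopes, an assumed micro share and an assumed role for the rating; the documents anchor none of the associations. This is a minor to moderate weakness with a nearly free remedy, not evidence that the PRolaCT-O result will be materially wrong. It does not extend to the HRQoL endpoint through baseline MHS.

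**What to change.** Replace the micro/macro term in the propensity model by maximum diameter in mm from the qualifying MRI, entered as a log or spline term. State that the 0.10 standardised-difference criterion and the balancing plots apply to continuous diameter. Micro/macro can still be reported descriptively.

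Optionally, name the qualifying prolactin value, as a multiple of the local upper limit, as a further confounder. Its timing relative to DA treatment must then be defined, because pre-treatment, on-treatment and post-withdrawal values do not mean the same thing.

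The main change takes a few words and no new data collection. The downside is slightly more variable weights.

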#### Exclusion criteria

Contraindication for one of the treatment modalities, e.g. severe side effects of DA treatment or DA-resistant prolactinomaContraindications to surgery, or a clear indication for surgical resectionPregnancy at the time of randomisationClinical diagnosis of acromegalyPrior radiotherapy of the pituitary gland areaSevere renal failure (eGFR < 30 ml/min)Insufficient understanding of the Dutch and English language

Patients eligible for participation in one of the RCTs, but do not consent to randomisation because there is a clear patient preference for either DA treatment or surgery, are considered for participation in PRolaCT-O, also see Fig. 1.

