### Treatment allocation

Within each RCT (PRolaCT-1, PRolaCT-2, or PRolaCT-3), participants are randomly allocated in a 1:1 ratio to either neurosurgical counselling (with potential subsequent surgery when desired) or standard care with DA. Randomisation is performed in blocks of sizes varying between 4, 6, and 8 patients and is stratified by sex to equally divide male participants and by tumour size (< 10 mm versus ≥ 10 mm). Randomisation is performed centrally in the LUMC using the built-in randomisation tool of the web-based database programme (Castor Electronic Data Capture (EDC), Castor, Amsterdam, the Netherlands). Investigators, treating physicians, and participants will not be blinded to the outcomes of randomization. With the use of varying block sizes, the allocation sequence is kept concealed by the randomisation programme. In PRolaCT-O, treatment choice, based on patient and physician preference, is solely recorded and may be DA treatment as a first- or second-line treatment, or surgical counselling as a second-line treatment (thus not in newly diagnosed patients). For all studies, the interpreters of MRIs, ophthalmologic assessments, and surgical difficulty will be blinded when possible. Unblinding will not occur.

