The study intervention in PRolaCT is thus the neurosurgical counselling rather than surgical intervention, which allows patients in the intervention groups to opt for surgery. If there is a substantial proportion of patients in the intervention group who do not undergo surgery, it would lead to an attenuation of found effects. Furthermore, as a part of standard care, participants in the control groups may still undergo surgery in the follow-up of the study (which is sporadically needed in case of severe DA intolerance or resistance). The expected cross-over between treatments was taken into account for the sample size calculation, resulting in a larger sample size needed. However, we anticipate that neurosurgical counselling greatly contributes to patients’ decision for a specific treatment, and therefore, our approach may decrease the risk of study drop-out due to disappointment over the outcome of randomisation.

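### The PRolaCT-O propensity model for surgical counselling includes preference recorded after counselling, which counselling itself influences

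*Protocol article*

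**What the plan says.** All references are to the protocol article.

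- **Exposure.** Under *Analyses in PRolaCT-O using propensity score methods*: "The propensity to receive surgical counselling will be estimated using logistic regression". The exposure is counselling, not surgery. *Treatment allocation* agrees: the options it records for PRolaCT-O are DA treatment or surgical counselling.
- **Covariates.** The same sentence lists, among the potential confounders, "patient and MDT treatment preference pre- and post-counselling (neutral, medication, or surgery".
- **Use of the score.** "Inverse probability weighting based on the propensity score will be used to balance the treatment groups". The reweighted groups are then compared as in the RCTs. Matching on the propensity score is the sensitivity analysis. Adequacy is judged by standardised mean differences below 0.10 and by balancing plots.
- **What counselling does.** *Intervention: surgical counselling* says that the consultation may end with the patient advised against surgery, and that the MDT may propose standard treatment on the strength of what it brings out. *Rationale for the study design* expects that "neurosurgical counselling greatly contributes to" the patient's treatment decision.
- **How patients enter and are treated.** *Exclusion criteria* directs to PRolaCT-O those eligible patients who "do not consent to randomisation because there is a clear patient preference for either DA treatment or surgery". *Treatment allocation* adds: "In PRolaCT-O, treatment choice, based on patient and physician preference, is solely recorded".

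**The concern.** A propensity score for an exposure should be built from variables that the exposure cannot have altered. A preference held after surgical counselling is not such a variable. It comes later than the exposure and, by the protocol's own account, is partly produced by it. It also lies on the path by which counselling is supposed to work: counselling changes preference, preference leads to surgery, and surgery changes remission and quality of life. Making the two groups alike on that variable removes the part of the effect that travels through it.

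The stated safeguards would not reveal this. Good balance on post-counselling preference would count as success, and matching on the same score carries the same error.

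There is a second consequence. Where counselling and later preference are strongly linked, few uncounselled patients prefer surgery, and those few receive large weights.

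PRolaCT-O is described under *Study design* as a fall-back for the primary objectives. The discussion of patient preference says that RCT recruitment has been limited so far and that PRolaCT-O should report earlier than the RCTs. Its result also enters the planned meta-analysis with the RCTs, so a bias here would be carried forward.

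**Working it through.** **1. The protocol's own figures.** From *Sample size calculation*: remission 90% v 50%, a 10-point difference with SD 16, up to 30% of the intervention arm not operated on, α 0.025, power 0.8.

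- Remission in the counselled arm: 0.7 × 0.90 + 0.3 × 0.50 = 0.78. Comparing 0.78 with 0.50 at two-sided α 0.025 gives 55 per arm, as stated.
- Mental health scale: 0.7 × 10 = 7 points. Then 2 × (16/7)² × (2.241 + 0.842)² ≈ 99.3, so 100 per arm. The t-based version gives 101, as stated.

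The protocol therefore defines the effect of counselling as the effect of surgery times the share who take it up. That is the path on which post-counselling preference sits.

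**2. Set-up of the illustration.** There are 110 counselled and 110 uncounselled patients (the PRolaCT-O target). Preference is reduced to surgery or not.

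- a = share of counselled patients who prefer surgery afterwards = 0.70 (the protocol's uptake).
- q = share of uncounselled patients who prefer surgery. It is not in the documents, so it is assumed from 0.02 to 0.20.
- The groups are otherwise comparable, so the gap between a and q is due to counselling.
- Only counselled patients who prefer surgery are operated on, and surgery is worth 10 points. The true effect is 10 × 0.70 = 7.0.

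**3. Estimate after weighting on post-counselling preference.** Weighting gives both groups the pooled preference share (a + q)/2. The estimate becomes 10 × (a + q)/2.

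**4. Weights.** With equal groups, P(counselled | prefers surgery) = a/(a + q). An uncounselled patient who prefers surgery has weight (a + q)/q. One who does not has weight (2 − a − q)/(1 − q). The effective size of the 110 uncounselled is (Σw)²/Σw² = 440 / [(a + q)²/q + (2 − a − q)²/(1 − q)].

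| q | Estimate (true 7.0) | Largest weight | Effective size of 110 |
|---|---|---|---|
| 0.02 | 10 × 0.72/2 = 3.6 | 0.72/0.02 = 36 | 16 |
| 0.05 | 10 × 0.75/2 = 3.75 | 0.75/0.05 = 15 | 34 |
| 0.10 | 10 × 0.80/2 = 4.0 | 0.80/0.10 = 8 | 55 |
| 0.20 | 10 × 0.90/2 = 4.5 | 0.90/0.20 = 4.5 | 79 |

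Worked line for q = 0.02: 0.72²/0.02 = 25.92 and 1.28²/0.98 = 1.67, so 440/27.59 = 15.9.

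**5. Limits of the illustration.** If counselling leaves preference unchanged (q = a = 0.70), the formula returns 10 × 1.40/2 = 7.0, so there is no bias. If preference alone decided surgery in both groups, the true effect would be 10 × (0.70 − q), that is 6.8 to 5.0 points for q = 0.02 to 0.20, and the weighted estimate would be 0.

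**6. Cross-check by simulation** (220 patients, 400 repetitions per setting, assumed strengths of association). Here prior preference also drives who is counselled. Both models include a baseline covariate and pre-counselling preference; one adds post-counselling preference.

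| Effect of counselling on preference | True | Without post-counselling preference | With it |
|---|---|---|---|
| None | 3.4 | 3.4 to 3.5 | 3.4 to 3.6 |
| Strong | 6.8 | 6.7 to 7.0 | 4.5 to 4.7 |

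In the strong setting, adding the variable raises the SD of the estimate from 2.1–2.8 to 5.5–6.7 and the median largest weight from 3.4–12.4 to 43–62. The effective size of the smaller group drops from 50–98 to 10–19.

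**The case against.** The strongest defence is that the word counselling is used in more than one sense. *Patient identification and enrolment* uses it for the discussion of study participation, and a preference recorded after that could precede the exposure. But the covariate stands in the same sentence as the propensity to receive surgical counselling, and the plain reading is that both mean the same event. If surgery received were taken as the exposure instead, post-counselling preference would come before it, but would almost determine it. The bias argument would lapse and the overlap problem would remain.

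The introductory such as leaves the covariate list open. That allows additions; it does not withdraw a covariate that is named.

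Four stronger readings are tempting, and the documents do not support them.

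- **Extreme weights are certain.** They depend on q, which is assumed. At q = 0.10 the largest weight is 8, and at 0.20 it is 4.5. Patients may also enter PRolaCT-O simply because they decline randomisation, and the preference scale has a neutral level.
- **Power collapses.** With half the effective size in each arm (50.5), power for the mental health scale would be 47% at 7 points, but 65% at 8.5 and about 80% at 10. Patients who choose counselling may take up surgery more often than 70%, and baseline adjustment may add precision. No single figure is defensible.
- **Post-counselling preference exists only for counselled patients.** The documents do not say so. The covariate includes the MDT's preference, and the MDT confirms eligibility for all.
- **Pre-counselling preference should go too.** It precedes the exposure and is a central source of the confounding by indication that the protocol expects. Removing it would trade one bias for another.

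It also stands that the RCT analyses are unaffected, and that the protocol says PRolaCT-O cannot replace them.

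**Conclusion.** The point holds for post-counselling preference. The protocol adjusts the effect of surgical counselling for something that counselling is expected to change, and its own diagnostics would not show the problem. In the illustration, a 7.0-point effect is estimated as 3.6 to 4.5 points, a loss of about 36% to 49%. Overlap ranges from poor at q = 0.02 to moderate at q = 0.10 and above.

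The 10 points and 70% uptake come from the protocol. The values of q, the rule for who is operated on and the simulated strengths of association are assumptions. The size of the bias therefore cannot be fixed from the documents. Its existence requires only that counselling shifts preference, which the protocol expects. In the scenarios examined it runs towards no effect.

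**What to change.** - Delete post-counselling patient and MDT preference from the propensity model, and state that the model uses only covariates fixed before the counselling decision. The blinded surgical-outcome rating is made later, but can stay if it rests on material that predates counselling.
- Keep pre-counselling patient and MDT preference as confounders.
- Report the distribution of the weights and the effective sample size per group beside the balance checks already planned.
- Use post-counselling preference descriptively only, for example to show how often counselling changed the intended treatment.

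The cost is a change of wording; no new data are needed. Pre-counselling preference may still strain overlap in a self-selected cohort: in the strongest simulated setting the median largest weight was about 12 and the smaller group's effective size about 50. Overlap weights could be added as a sensitivity analysis. They are not required, and they shift the target to patients with a realistic chance of either treatment.

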### Sample size calculation

To detect a difference in remission rate at 36 months of 40% between surgery (expected rate 90%) and medical treatment (expected rate max. 50%), with a power of 0.8 and an *α* of 0.025, 55 patients per treatment group arm are needed, when considering that max. 30% in the interventional arm will not undergo surgery. However, to detect a difference of 10 points at the SF-36 mental health scale at *T* = 12 with an *α* of 0.025 and a power of 0.8, assuming that the standard deviation is 16, based on the general population [31], and that max. 30% of the interventional arm does not undergo surgery, at least 101 patients per treatment arm are needed. To compensate for the loss to follow-up, it is aimed to include 110 patients per treatment arm and therefore 220 patients in total per RCT/PRolaCT-O (aiming for at least 110 patients per treatment group in PRolaCT-O). If patient recruitment would prove challenging, and the required sample size for separate analyses of the RCTs cannot be reached for two or more of the RCTs (PRolaCT-1, PRolaCT-2, or PRolaCT-3) within the duration of the study, the planned analyses could be performed using the combined sample size for two to three RCTs of 220 patients.

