#### Main endpoints

##### Health-related quality of life

In the three RCTs, the difference between the two treatment arms in MHS of the SF-36 will be compared at 12 months using a linear regression analysis, using treatment and the baseline measurement as covariates (analysis of covariance).

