##### Disease remission

In the three RCTs, the percentage of patients that achieve disease remission at 36 months will be calculated for the two treatment arms with corresponding 95% confidence interval and compared using a chi-square test.

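### Read literally, PRolaCT-O applies the RCT chi-square test and linear regression to inverse-probability-weighted data; the plan should name a variance estimate that is valid under weighting

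*Protocol article*

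**What the plan says.** In the protocol article, the section on propensity score methods in PRolaCT-O sets the weighting step: "Inverse probability weighting based on the propensity score will be used to balance the treatment groups". The next sentence sets the comparison: "After observations are reweighted, treatment groups are compared in the same way as in the RCTs".

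The RCT methods are defined just before, under Main endpoints:
- Remission at 36 months: percentages "will be calculated for the two treatment arms with corresponding 95% confidence interval and compared using a chi-square test".
- MHS at 12 months: compared "using a linear regression analysis, using treatment and the baseline measurement as covariates (analysis of covariance").

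The section Planned statistical analyses sets the significance threshold at p < 0.02. The Sample size calculation gives PRolaCT-O the same target as an RCT, "aiming for at least 110 patients per treatment group in PRolaCT-O".

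No robust, sandwich, survey-type or bootstrap variance is named for the weighted comparison. The only bootstrap in the article belongs to the economic evaluation. Whether the weights are stabilised or truncated is not stated.

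**The concern.** A Pearson chi-square statistic assumes that each cell is a count of independent patients. Inverse probability weights are not counts. Raw weights, 1/e for one group and 1/(1 − e) for the other (e being the propensity score), sum to about twice the number of patients, so the statistic is roughly doubled. Stabilised weights remove the doubling but not the effect of unequal weights. Weighted linear regression with model-based standard errors shares that second defect.

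Unequal weights are a realistic prospect here. The propensity model includes patient and multidisciplinary-team treatment preference before and after counselling, which may come close to determining treatment. The Discussion itself expects confounding by indication.

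PRolaCT-O also matters to the programme. Study design describes it as a fall-back for the primary and secondary objectives if recruitment is difficult. The Discussion reports that recruitment has been limited and expects PRolaCT-O to report before the RCTs. Its results also enter a meta-analysis with the RCTs. If that meta-analysis weights by inverse variance, understated standard errors would give the non-randomised cohort too much influence.

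**Working it through.** **1. The plan's own figures.** The article gives no error rate or precision for the weighted analysis. Its sample sizes can be reproduced with α = 0.025 taken as two-sided (z = 2.241) and power 0.8 (z = 0.842).
- Remission: 30% not operated gives 0.7 × 90% + 0.3 × 50% = 78% against 50%, pooled 64%. n = [2.241 × √(2 × 0.64 × 0.36) + 0.842 × √(0.78 × 0.22 + 0.50 × 0.50)]² / 0.28² = 54.5, so 55 per arm, as stated.
- MHS: 0.7 × 10 = 7 points, SD 16. The t-test solution is 100.6, so 101 per arm, as stated.

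These figures stand.

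**2. Doubling alone, by hand.** A two-sided test at 0.02 uses z = 2.326. If the chi-square statistic is doubled, the true error is 2 × [1 − Φ(2.326/√2)] = 2 × [1 − Φ(1.645)] = 0.10. That is five times the threshold, before any variability in the weights is counted.

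**3. Simulation.** Inputs from the article: 220 patients (2 × 110) and the 0.02 threshold. Assumed: no treatment effect; four independent standard-normal confounders; treatment log-odds with standard deviation 0.5, 1.0 or 1.5 (weak, moderate, strong); remission about 50% and dependent on two confounders; MHS dependent on baseline and confounders. The propensity score is estimated by logistic regression, with 3000 repeats per setting. Mean effective sample size was 201, 165 and 128, that is 91%, 75% and 58% of 220.

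Type I error at 0.02:

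| Method | Weak | Moderate | Strong |
|---|---|---|---|
| Chi-square, raw weights as counts | 0.092 | 0.149 | 0.221 |
| Chi-square, stabilised weights | 0.018 | 0.041 | 0.083 |
| Weighted regression, model-based SE | 0.023 | 0.035 | 0.086 |
| Weighted risk difference, robust SE | 0.015 | 0.019 | 0.023 |
| Weighted regression, robust SE (HC3) | 0.016 | 0.014 | 0.016 |

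The Monte Carlo standard error is at most √(0.22 × 0.78/3000) = 0.008.

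At 0.05, model-based weighted regression rejected in 0.053, 0.082 and 0.141 of datasets, so its 95% intervals cover about 95%, 92% and 86%. With HC3 the rejection rates were 0.040, 0.035 and 0.042.

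**4. Sensitivity to the assumed confounding.** Two further simulations of the same kind (220 patients, no effect, weak/moderate/strong) gave, at 0.02:
- raw-weight chi-square: 0.10/0.12/0.17 and 0.11/0.15/0.22;
- stabilised chi-square: 0.022/0.027/0.062 and 0.020/0.046/0.098;
- model-based weighted regression: 0.073 under strong confounding in one, 0.014/0.034/0.104 in the other;
- robust variance: 0.013 to 0.019 in one, about 0.01 to 0.03 in the other.

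**5. Power after weighting.** Weighting lowers the effective sample size, so power was checked on the plan's assumptions (α 0.025, 101 per group after losses).
- Remission: power = Φ{[0.28 × √n − 2.241 × √(2 × 0.64 × 0.36)] / √(0.78 × 0.22 + 0.25)}. At effective fractions of 80%, 70%, 64% and 58% this gives 94%, 90%, 87% and 83%.
- MHS, t-test with d = 7/16: at fractions of 90%, 80% and 70%, power is 75%, 70% and 63% without baseline adjustment. The plan adjusts for baseline, which divides the SD by 1/√(1 − r²) for baseline correlation r. For r = 0.3 power is 80%, 74% and 68%; for r = 0.5 it is 87%, 83% and 77%; for r = 0.6 it is 92%, 89% and 84%.

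**The case against.** The strongest reply is that the article never calls for an unmodified test. Comparing groups as in the RCTs can mean the same contrast and model, fitted with weights and a suitable variance. The choice of variance estimator and of stabilised weights is detail that a condensed article commonly leaves to a full protocol or analysis plan. The article already gives the confounder list, a balance criterion and a matching sensitivity analysis. The highest error rates need raw weights entered as patient counts, which the article does not choose.

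Much of this stands. It rules out the stronger reading, that the PRolaCT-O p-values and intervals will necessarily be wrong. With stabilised weights and weak confounding both tests ran close to nominal, and every confounding strength used here is assumed.

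The reply does not remove the point, because the article is not merely silent. It carries named methods over to the weighted data, and for remission the named method is a test: "compared using a chi-square test". That test has no valid direct form on weighted counts. An analysis plan that followed the sentence literally would be wrong, and one that used a valid method would depart from its literal reading.

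A reader might also infer that PRolaCT-O cannot deliver the stated power, since its target makes no allowance for weighting. The documents do not support this. Remission needs 55 per group and at least 110 are planned, so power stays above 80% throughout the range examined. For MHS a shortfall is possible, but it depends on the effective sample size and on the baseline correlation, and the article gives neither.

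**Conclusion.** The point holds in a conditional form. Read literally, the comparison sentence applies a chi-square test and a linear regression to weighted data without a variance that reflects the weighting. At the 0.02 threshold the type I error is then about 0.09 to 0.22 for chi-square on raw weights. With stabilised weights or model-based weighted regression it runs from about nominal to about 0.06 to 0.10. Robust variance gives about 0.01 to 0.03. These ranges rest on 220 patients, a correctly specified propensity model and assumed confounding; they are not figures from the documents. The upper ends require strong confounding, which is plausible given the preference variables in the propensity model but is not established.

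The RCT analyses and the sample sizes of 55 and 101 are not affected. The Discussion says that PRolaCT-O cannot replace the RCTs, which limits the consequence, but its fall-back role and its place in the meta-analysis make the correction worthwhile.

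**What to change.** Replace the comparison sentence in the PRolaCT-O propensity score section with a rule along these lines:
- Remission at 36 months: inverse-probability-weighted risk difference.
- MHS at 12 months: weighted linear regression on treatment and baseline MHS.
- Both with sandwich standard errors, or a bootstrap that re-estimates the propensity score in every resample.
- P-values, confidence intervals and the standard errors passed to the meta-analysis all come from these.
- No Pearson chi-square test on weighted counts.

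It would also help to state whether weights are stabilised and to report the effective sample size.

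The cost is one or two sentences and a few lines of code, settled before analysis. Recruitment, data collection and the RCT analyses do not change. Where the weights vary strongly, the PRolaCT-O intervals will be wider than the literal reading would give.
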